### Data monitoring

#### Steering Committee and Data Safety Monitoring Board

All collaborators, site investigators, and research staff serve on the Trial Steering Committee. The committee aims to meet via teleconference every 6 months.

The DSMB has full responsibility for the monitoring of response variables for adverse events throughout the trial. This committee functions independently from all other study committees and serves in an advisory role to the Executive Committee. The DSMB consists of three individuals, covering requisite expertise in clinical epidemiology, biostatistics, urologic oncology, and anesthesia, and may consult external experts regarding specific outcome evaluations.

#### Stopping rules

No early stopping rules have been developed for this trial; early stopping criteria are at the discretion of the members of the independent DSMB. The DSMB may make recommendations to terminate or continue the study. Early stopping of the study will only be based on appraisal of SAEs and will be at the discretion of the clinical experts of the independent DSMB.

#### Individual discontinuation criteria

In the event of an anaphylactic reaction to the allocated agent, the attending anesthesiologist will stop the intervention and will treat the anaphylaxis without un-blinding the allocated agent.

#### Harms

Adverse events are documented as part of the CRFs. Severe adverse events are submitted to the central coordinating center using a study-specific reporting form. We do not expect any issues with safety, thus no formal interim analyses and stopping rules have been planned; however, having built-in independent safety oversight is prudent. Adverse events are reported to Health Canada as per International Conference on Harmonization/Good Clinical Practice (ICH-GCP) and Health Canada Division 5 regulations.

#### Summary of the known and potential risks and benefits to participants involved in the trial

Smoking is a common risk factor for bladder cancer and cardiovascular disease, thus many bladder cancer patients are at risk for thromboembolic complications such as MI, stroke, DVT, and PE. As outlined, given the mechanism of action of tranexamic acid, that being the inhibition of clot breakdown, it could be anticipated that this medication would increase the risk of thromboembolic events. Contrary to this notion, previous studies of tranexamic acid with enrollment of thousands of patients with cardiovascular disease have not observed an increased risk of these adverse events [12].

Tranexamic acid has been approved for use by Health Canada and has a well-established side-effect profile [17]. Tranexamic acid is used predominantly in cardiac surgery, but has also been studied in orthopedic surgery and trauma patients [18]. A recently updated systematic review of lysine analogs (including tranexamic acid) identified 252 trials, of which 173 were conducted in cardiac surgery and 53 in orthopedic surgery [12]. Data regarding adverse effects of tranexamic acid was drawn from this Cochrane systematic review as well as a recent randomized controlled trial (RCT) examining the use of tranexamic acid in a trauma setting [18]. The Cochrane review of anti-fibrinolytics identified 65 trials containing 2528 patients comparing tranexamic acid with placebo to prevent blood loss and transfusion [12]. However, none of the trials in this systematic review included patients treated with radical cystectomy. From this review of RCTs, the risk of red blood cell transfusion was 39% lower among patients who received tranexamic acid compared to placebo or standard of care (RR 0.61; 95% CI 0.53 to 0.70).

The use of tranexamic acid was not associated with increased risk of death (RR 0.60, 95% CI 0.33 to 1.10), MI (RR 0.79, 95% CI 0.41 to 1.52), or stroke (RR 1.23, 95%CI 0.49 to 3.07). Tranexamic acid was not associated with increased risk of developing a DVT (RR 0.71, 95% CI 0.35 to 1.43) or a PE (RR 0.67, 95% CI 0.23 to 1.99). Treatment with tranexamic acid did not appear to increase the risk of developing renal failure or dysfunction (RR 0.89, 95% CI 0.33 to 2.37). The CRASH-2 trial randomized 20,211 adult trauma patients to tranexamic acid or placebo [18]. In this trial, there were 33 deaths (0.3%) in the tranexamic acid arm vs. 48 (0.5%) in the placebo arm related to vascular occlusion (*p* = 0.96) including 7 vs. 22 deaths from MI, 8 vs. 5 from stroke, and 18 vs. 21 from PE, respectively. Vascular occlusive events, fatal or non-fatal, did not differ significantly with 168 (1.7%) patients with one or more vascular occlusive events (MI, stroke, PE, DVT) in patients receiving tranexamic acid vs. 201 (2%) in patients receiving placebo (RR 0.84, 95% CI 0.68 to 1.02).

In a retrospective study of 604 patients undergoing cardiac surgery [19], it was reported that post-operative seizures occurred significantly more frequently in patients treated with tranexamic acid compared to epsilon-aminocaproic acid. Twenty-one tranexamic acid-treated patients (7.6%) compared to 13 (3.3%) epsilon-aminocaproic acid-treated patients (*p* = 0.019) developed post-operative seizures. There was no control group in this study to which comparisons could be made. Patients in this study received a high dose of tranexamic acid with an initial 2-g bolus at the beginning of cardiopulmonary bypass followed by infusion of 0.5 g/h until chest closure and 2 g added to the priming fluid of the cardiopulmonary bypass system. Other recent retrospective studies have also shown that tranexamic acid, when given in high doses of 61 to 259 mg/kg, is associated with elevated rates of post-operative seizure compared to epsilon-aminocaproic acid [20, 21]. We have not found data indicating increased risk of seizure in trials using a similar dose to what we have chosen for our trial.

Finally, the recent tranexamic acid RCT of 200 radical prostatectomy patients used a comparable dose to our study (500 mg loading and 250 mg/h infusion). They captured adverse events at 1 and 6 months following surgery [22]. No deaths occurred and thromboembolic events were more common in the control group (five in the placebo vs. two in the tranexamic acid arm; RR 0.4; 95%CI 0.09 to 1.74).

Given the effectiveness of tranexamic acid in reducing blood loss during other surgical procedures without increasing the number of thromboembolic events compared to placebo, we hypothesize that tranexamic acid will eliminate the need for transfusion in a significant proportion of patients, reduce overall blood utilization, and not result in increased incidence of adverse events. Despite the large volume of evidence establishing safety of tranexamic acid in cardiac and orthopedic surgical patients, we acknowledge the theoretical risks and, therefore, we are monitoring vascular occlusive events, seizures, and other potential serious adverse reactions.

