### Sample size

A patient record review from The Ottawa Hospital indicated that red blood cell transfusions were performed in approximately 60% of patients with bladder cancer undergoing radical cystectomy. However, we anticipate that transfusion rates are likely to decrease slightly while under the study protocol. From the results of our survey, systemic anti-fibrinolytics are rarely used during radical cystectomies; to influence practice we suggest that tranexamic acid will have to produce a substantial reduction in the proportion of patients requiring transfusion. To assist in determining the minimally important effect of tranexamic acid deemed necessary to change clinical practice, Canadian experts in the surgical treatment of bladder cancer were surveyed in February 2012. Minimally important effect sizes ranged from an absolute difference of 15% (relative risk (RR) 30%) to 30% (RR 60%) and are consistent with effects observed in many clinical trials of tranexamic acid [12]. From our systematic review of lysine analogs to prevent bleeding during pelvic surgery, the pooled estimate favored lysine analogs (RR 0.69; 95% confidence interval (CI) 0.47 to 1.00) [13].

If 50% of placebo patients will require at least one transfusion within 30 days of surgery, and if the use of tranexamic acid reduces the need for transfusion within 30 days to 35% of patients (15% absolute reduction), and assuming 80% power to detect this absolute difference, with a two-sided alpha level of 5%, the required sample size is 340 people (170 per treatment group). To account for 2% non-compliance with the protocol (possibly due to intraoperative complications or protocol deviations) the total sample size required was estimated to be 354 patients (177 per arm) [15].

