### Statistical methods

Patient baseline characteristics will be summarized with descriptive statistics. Comparative analyses will be based on an intention-to-treat principle (i.e., based on the participant’s randomized study arm allocation). To address the primary objective of the effect of systemic tranexamic acid compared to placebo on the proportion of patients requiring red blood cell transfusion within 30 days, a chi-square test of proportions will be used. The effect size will be derived with an unadjusted RR and 95% confidence limits. If notable baseline imbalances are present, an adjusted estimate will be derived for the RR by stratifying on the potential confounders and pooling with a Mantel-Haenszel RR estimator. Secondary analyses of the effect of tranexamic acid on the volume of intraoperative blood loss and the perioperative adverse event rate will follow in a similar fashion, using chi-square or *t* tests, depending the outcome, and logistic or linear regression to estimate the magnitude of effect. A Poisson regression model will be fit to assess the difference in the number of transfused blood products between trial arms. Subgroup analyses will also be presented for clinically important baseline factors that may influence the effect of the drug, including sex, patient age (< 60 years, 60–70 years, 71–80 years, and < 80 years), preoperative hemoglobin (< 100 g/L, 100–120 g/L, and > 120 g/L), and previous history of cardiac disease (yes/no). Data is compiled by the study statistician and reviewed by an independent DSMB every 6 months. No interim analysis is planned for this trial.

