At the completion of the trial, we will better understand the benefits and risks of systemic tranexamic acid during radical cystectomy. Specifically, we will know if tranexamic acid reduces the risk of exposure to blood transfusion among patients undergoing radical cystectomy. Given that there are few exclusion criteria and multi-institutional involvement, we expect our findings to have broad applicability. As this is the first RCT evaluating the use of a systemic anti-fibrinolytic during radical cystectomy, the findings may have an immediate impact on patient care. If the study is negative, we can avoid unnecessary exposure of patients to tranexamic acid during radical cystectomy. If the study reveals a benefit of tranexamic acid, we will change our standard of practice regarding radical cystectomy procedures, and procedures common to other major pelvic surgeries associated with significant blood loss will be challenged (Additional file 1).

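### A non-significant primary result would not by itself show lack of worthwhile benefit, and the no-increase safety hypothesis has no margin or precision target behind it

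*Protocol article*

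**What the plan says.** **Efficacy.** The Sample size section sets the planning case: "If 50% of placebo patients will require at least one transfusion within 30 days of surgery" and tranexamic acid "reduces the need for transfusion within 30 days to 35% of patients (15% absolute reduction", then "with a two-sided alpha level of 5%, the required sample size is 340 people (170 per treatment group", and after a 2% allowance for non-compliance, "the total sample size required was estimated to be 354 patients (177 per arm". Fifteen points is also the lower end of what surveyed experts said would change practice: "Minimally important effect sizes ranged from an absolute difference of 15% (relative risk (RR) 30" per cent, up to 30 points. The primary analysis is a chi-square test with an unadjusted relative risk and 95% limits. The Discussion then states what a null result would mean: "If the study is negative, we can avoid unnecessary exposure of patients to tranexamic acid during radical cystectomy".

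**Safety.** The section on known and potential risks and benefits hypothesises that the drug will "reduce overall blood utilization, and not result in increased incidence of adverse events". Under Statistical methods, the analysis of blood loss and "the perioperative adverse event rate will follow in a similar fashion, using chi-square" or t tests, with logistic or linear regression for the size of the effect. Thrombotic events are singled out in the secondary objectives. The only sample-size calculation shown is for transfusion.

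**The concern.** Both statements are about absence: no benefit worth having, and no added harm. A test of difference that fails to reach significance does not establish either. What matters is whether the confidence interval excludes the effect of interest. For efficacy, the article names that effect (15 points) but does not connect it to the reading of a negative trial. For safety, it names none.

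Two errors become possible. The drug could be set aside when the data remain compatible with the benefit that the trial was built to find. Or a hypothesis of no increase could appear confirmed when the data remain compatible with a doubling of thrombosis or more, in patients whom the Discussion describes as being at high risk of such events.

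**Working it through.** **1. The plan's own figure.** Inputs from Sample size: 50% against 35%, 80% power, two-sided 5%, 1:1 allocation. With pooled variance under the null and no continuity correction, mean proportion 0.425:

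n = [1.96 × √(2 × 0.425 × 0.575) + 0.8416 × √(0.50 × 0.50 + 0.35 × 0.65)]² / 0.15² = 169.3, so 170 per arm.

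170 / 0.98² = 177.0 per arm, or 354. Both stated figures reproduce. Power at 177 per arm is 82% by this approximation.

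**2. Which non-significant results still contain 15 points?** Take placebo at 89/177 (50.3%), the nearest count to 50%, with all 177 per arm analysed. The p-value is from the uncorrected chi-square test. The interval is d ± 1.96 × √(p₁(1-p₁)/177 + p₂(1-p₂)/177).

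| Transfused on drug | Reduction (points) | p | 95% interval (points) |
|---|---|---|---|
| 70/177 | 10.7 | 0.042 | 0.4 to 21.0 |
| 71/177 | 10.2 | 0.055 | -0.1 to 20.5 |
| 75/177 | 7.9 | 0.14 | -2.4 to 18.3 |
| 80/177 | 5.1 | 0.34 | -5.3 to 15.5 |
| 81/177 | 4.5 | 0.39 | -5.9 to 14.9 |

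From 71 to 80 transfused on the drug, the result is non-significant and the interval contains 15. From 81 upward, the interval excludes 15.

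**3. How often would this happen?** Enumerating all pairs of binomial counts at 177 per arm with true rates of 50% and 35%, and applying the same test and interval: the probability of a non-significant result is 0.187, about 19%. Among those results, 87% have an interval that contains 15 points. So 0.187 × 0.87 ≈ 0.16 of all such trials would be negative without excluding the planned effect.

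**4. Safety precision.** The article gives no thrombotic event rate for cystectomy, so two rates are assumed:
- 2%, the placebo figure for vascular occlusive events in the trauma trial that the article cites.
- 5%, from five placebo events in the prostatectomy trial of 200 patients, if those were split 100 and 100. The article does not give the arm sizes.

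With equal observed rates and e events per arm, SE(log RR) = √(2/e - 2/177):
- 2%: e = 3.54, SE = 0.744, upper limit exp(1.96 × 0.744) = 4.3.
- 5%: e = 8.85, SE = 0.463, upper limit exp(1.96 × 0.463) = 2.5.

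On the absolute scale, the half-width 1.96 × √(2p(1-p)/177) is 2.9 points at 2% and 4.5 points at 5%.

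**5. Label check.** 35/50 = 0.70 and 20/50 = 0.40. The 30% and 60% printed after the abbreviation RR, defined there as relative risk, are relative risk reductions.

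**The case against.** **On efficacy.** The sentence sits in a Discussion and is not an analysis rule. Systemic drugs of this kind were used by only 5% of surveyed surgeons, and the article says that uncritical use is not warranted without definitive evidence. Declining to adopt an unproven drug is not the same as claiming that benefit has been excluded. The trial also has its planned power for the smallest effect in its own survey. All of this is fair, and it keeps the point to one of wording. But the sentence calls exposure after a negative result unnecessary, which is a conclusion about benefit, and it sets no condition on the interval.

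**On safety.** A reader might infer that the plan will report a non-significant adverse-event test as proof of safety. The article does not say so. It states a hypothesis, acknowledges the theoretical risk, monitors vascular occlusive events and seizures, and plans effect estimates as well as tests. Details may also be in an analysis plan that is not shown. What stands is narrower: the article states a hypothesis of no increase and gives no margin or precision by which to judge it.

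**Other tempting readings that fail:**
- That 177 per arm can support neither conclusion. An observed reduction below about 5 points would exclude 15. With no observed excess, added harm above roughly 3 to 5 points would be excluded at 2% to 5% rates.
- That chi-square and logistic regression are invalid here. The uncorrected test has true size 0.045 at a 2% rate and 0.049 at 5%. An arm with no events, which would leave the logistic estimate without a finite value, has probability 5.5% at 2% and 0.02% at 5%. Small-count methods are ordinary analysis-plan content, and Fisher's test would lower power against a doubling (43% to 35% at a 5% rate; 18% to 11% at 2%).
- That the relative-risk label undermines the sample size. The calculation uses 50% and 35% and reproduces exactly.

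**Conclusion.** The point holds as a matter of interpretation, not of design or choice of test. A negative primary result would leave the 15-point effect open whenever the observed reduction lies between about 5 and 10 points. Under a true 15-point effect, about 19% of trials would be non-significant, and about 87% of those would not exclude 15. These figures assume 50% transfusion on placebo, 177 analysed per arm and simple large-sample intervals.

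The no-increase hypothesis rests on data that, with equal observed rates, could not exclude a relative risk of about 4.3 (2% rate) or 2.5 (5% rate). These limits depend on assumed rates borrowed from trauma and prostatectomy patients, and would be tighter if thrombosis after cystectomy is more frequent. The relative-risk label is a minor slip with no numerical consequence.

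**What to change.** 1. **Discussion:** conclude no worthwhile benefit only if the 95% confidence interval for the absolute reduction in transfusion excludes 15 points. Otherwise call a non-significant result inconclusive.
2. **Statistical methods, and the risk and benefit section:** state that the safety hypothesis will be judged on the 95% confidence interval for thrombotic events, in particular its upper limit, and not on non-significance.
3. **Sample size (minor):** relabel the 30% and 60% as relative risk reductions, or give them as RR 0.70 and RR 0.40.

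The cost is wording only: no new patients, data or tests. The downside is that claims after a null result become less favourable or less definite.

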### Auditing

#### Compliance with study allocation

In this study, compliance refers only to receiving the study intervention administered during the intraoperative period, under supervision by attending urologists and anesthesiologists. We classify patients as being fully compliant if the patient is administered a complete dose schedule of the allocated agent (tranexamic acid or placebo), partially compliant if the patient is administered an incomplete dose schedule of the allocated agent, and non-compliant if the patient does not receive the allocated agent. Reasons for partial and non-compliance may range from errors in randomization/drug administration, physician and pharmacy errors in allocation, intraoperative complications, death, etc. Compliance is not based on patient tolerance and is very likely to be random. We expect partial/non-compliance to be less than 1%, although our sample size adjustment accounts for a total of 2% partial compliance and non-compliance. The degree of compliance is documented in the intraoperative CRF. Any partial compliance or non-compliance requires additional documentation by way of the Protocol Deviation or Protocol Violation Form.

#### Loss to follow-up

We expect complete follow-up at hospital discharge and at 30 days postoperative given the complexity of care and necessary short-term follow-up. From past experience in a high-risk cardiac population [23] and given the captive patient population, we expect greater than 95% follow-up at 1 month. In a recently published trial of radical prostatectomy patients, all 200 patients completed follow-up [22].

### Monitoring procedures

Study monitoring is a sponsor responsibility as outlined in ICH-GCP. This responsibility has been delegated back to the qualified investigator as per N2 standard operating procedure (SOP) 901.001.

The qualified investigator assigns a suitably trained monitor to perform study monitoring at all participating sites. The monitor is not directly involved in the study. The monitor is trained on ICH-GCP, Health Canada Division 5 Regulations, Tri-Council Policy Statement: Ethical Conduct for Research Involving Humans (TCPS2), study protocol, OHRI SOPs, and study-specific procedures.

#### Site monitoring

The trial data, compliance, and adverse events are rigorously monitored using both remote and on-site methods of surveillance. This ensures that trial-related data is accurate, complete, and verifiable from source documents and that participant rights and safety are protected. The monitor verifies compliance with the regulatory requirements, protocol, GCP, study-specific procedures, and participant eligibility. In addition to evaluating the reported data for accuracy and completeness, the monitor identifies any trends in data that may be indicative of insufficient documentation or protocol deviations. Discrepancies noted in the data are recorded and the site is informed of all observations in the subsequent monitoring report.

The site monitor addresses deficiencies to the appropriate study team member in order to implement corrective actions or to recommend follow-up procedures. All observations noted during the monitoring visit appear in the monitoring report. The monitor assesses study files and documentation against ICH-GCP, regulatory requirements, protocol, OHRI SOPs and any study-specific SOPs.

#### Interim monitoring visits

To ensure patient safety and data integrity, regular remote monitoring visits are performed for each study site. If remote monitoring shows discrepancies in data or lack of compliance with regulations, or if requested by the DSMB or the site investigator, on-site monitoring is performed. The study monitor assesses: CRF source data verification (SDV), patient eligibility and consent, study-specific SOPs, delegation logs, SAEs for recording and reporting completeness, regulatory documentation (for site and/or sponsor), training documents, protocol-defined endpoints, essential document maintenance, deviation/violation recording and reporting, drug accountability, privacy considerations, and any protocol-specific procedures.

For remote monitoring, de-identified data from each site is sent to the monitor 6 months after site activation via secured courier. All data to be couriered is checked by the site coordinator prior to sending in order to ensure that patient privacy and confidentiality is maintained. No identifying materials are sent off-site. Documentation sent to the monitor for remote SDV includes: copies of signed and dated de-identified laboratory assessments, copies of signed and dated de-identified patient assessment forms (CRFs) with corresponding de-identified source documents, copies of de-identified source documentation that supports subjects’ eligibility to be enrolled into the study, copies of de-identified Investigator progress notes regarding patient-related decisions, signed and dated training logs as well as copies of materials used to train study staff (slide presentations, hand-outs).

